**Phase II**

The primary outcome in Phase II in this study is:

- The incidence of patient recovery infusing adoptive NK cells or adoptive memory T cells.
- **Recovery is defined as:** Proportion of participants in each group with normalization of fever and oxygen saturation [criteria for normalization: temperature < 38°C armpit, and SpO2 > 94%, sustained for at least 24 hours] or lymphopenia recovery **through Day 14.**

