**Phase II:**

Patients with SARS-CoV-2+ pneumonia or lymphopenia **and** O_2_Sat ≤ 94% on room air at screening, requiring or not oxygen supplementation (nasal cannula, oxygen mask with reservoir, non-invasive ventilation, etc) but **excluding** mechanical ventilation, will be selected.

- **Arm A**. Patients will be randomized to receive one of the following treatments:
  - Standard of Care Treatment (SoC)
  - SoC + RP2D for memory T cells
- **Arm B.** Patients will be randomized to receive one of the following treatments:
  - Standard of Care Treatment (SoC)
  - SoC + RP2D for NK cells

Phase II will begin once RP2D is established based on Phase I data.

Those patients showing clinical improvement at day 7 according to the investigator (based on respiratory status and blood-test results) who haven’t shown previous toxicities of grade 3 or higher, can receive a second cycle with the same dose at Day 7, if the investigator considers it appropriate.

See **Figure 2** for a schematic representation of the infusion regimen at each stage.

Figure2: Study scheme

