**Statistical analysis.**

The crude probability of recovery at 14^th^ day will be compared by Chi-Square test. A covariate‐adjusted estimation of the ratio of probability of recovery in experimental treatment to standard of care will be based on the standardization approach of Ge et al. (2011; Ge, M., Durham, L.K., Meyer, R.D., Xie, W. and Thomas, N. (2011) Covariate‐adjusted difference in proportions from clinical trials using logistic regression and weighted risk differences. Drug Information Journal, 45, 481–493). Covariates to be included will be age, sex, basal punctuation in WHO scale at baseline and presence of cardiovascular risk factors.

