******Figure 1. Schematic representation of procedure for blood donor obtention**

## Inclusion criteria

Patients eligible for inclusion in this study have to meet all of the following criteria:

- Male or female patients ≤ 80 years of age.
- Patient with diagnosis of COVID-19 infection with laboratory confirmation by reverse-transcription PCR (RT-PCR) of SARS-CoV-2 or other methods used according to each center protocol prior to study entry.
- Onset of symptoms < 12 days prior to administration of study treatment.
- **Phase I criteria:** Patients requiring hospitalization for COVID-19, with **pneumonia** diagnosed with chest radiograph or computed tomography imaging or **lymphopenia** (absolute lymphocyte counts below 1.2 x 10^9^cells /L) **AND** O_2_Sat ≤ 94% on room air at screening, no oxygen requirement or with an oxygen need of **≤ 2.5 lpm** in nasal cannula.
- **Phase II criteria:** Patients requiring hospitalization with **pneumonia** diagnosed with chest radiograph or computed tomography imaging or **lymphopenia** (absolute lymphocyte counts below 1.2 x 10^9^cells /L) **AND** O_2_Sat ≤ 94% on room air at screening, requiring or not oxygen supplementation (nasal cannula, oxygen mask with reservoir, non-invasive ventilation, etc), but **excluding** mechanical ventilation.
- Have a negative pregnancy test documented prior to enrollment (for females of childbearing potential).
- Be willing and able to comply with study procedures.
- Patients with the ability to comprehend and sign the informed consent
- Written informed consent obtained prior to any screening procedures.

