## Schedule of activities phase II

Table 3: Schedule of activities Phase II

| All the visits have a window of +/- 1 day | **Screening/D0** | **D1-D90 or until discharge** | **D7** | **D 14** | **D 21** | **D 28** | **D 90** |
| --- | --- | --- | --- | --- | --- | --- | --- |
| **Informed Consent** | x |  |  |  |  |  |  |
| **SARS-CoV-2 PCR testing** |  |  | x | x | x | x | x |
| **Medical history** | x |  |  |  |  |  |  |
| **Concomitant medications** | x | x | x | x | x | x | x |
| **Physical examination** | x | x | x | x | x | x | x |
| **Vital signs** | x | x | x | x | x | x | x |
| **Respiratory status** | x | x |  | x | x | x | x |
| **Hematology** | x | X^3^ (day 3) | x | x | x | x |  |
| **Biochemistry** | x | X^3^ (day 3) | x | x | x | x |  |
| **Markers of immunological function^1^** | x |  | x | x | x | x | x |
| **Blood sample for additional investigational studies** | x | X (day 3) | x | x | x | x |  |
| **Donor chimerism** |  | X^2^ (day 3) | x | X^2^ | X^2^ | X^2^ |  |
| **Pregnancy test** | x |  |  |  |  |  |  |
| **Scales (NEWS and 7 point scale)** | x | x | x | x | x | x | x |
| **Evaluation of patient recovery** |  |  |  | x |  |  |  |
| **Improvement according to investigator/Second dose^**^** |  |  | x |  |  |  |  |
| **Adverse events** | x | | | | | | |

^1^ Performed at screening and weekly. Please review section 7 for specific assessments.

^2^ Day: 3 and 7. If donor chimerism persists by day 7, repeat on days 14, 21, 28 and then continue weekly (until disappearance). Stop once it is negative.

^3^Day 3

^**^ Those patients showing clinical improvement at day 7 according to the investigator (based on respiratory status and blood-result tests) who have not shown previous toxicities of grade 3 or higher **and** if donor chimerism doesn´t persist, can receive a second cycle with the same dose at Day 7, if the investigator considers it appropriate.

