# General considerations

Tabular summaries will be presented by treatment group.

Categorical data will be summarized by number and percentages. Continuous variables will be summarized by descriptive statistics. Recover incidence (RI): Time to recovery.

The overall survival rate will be calculated by the nonparametric Kaplan-Meier method. Fisher exact test will be used to identify those patient characteristics that are significantly associated with treatment response (complete or partial).

For quantitative characteristics a chi-squared trend test will be conducted to examine whether the proportion of patients responding to treatment either increased or decreased across the levels of the characteristic.

The results of the statistical analysis will be displayed in the tables and as mean ± SD in the Figures. Levels of significance will be expressed as p-values (*p < 0.05).

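### Phase II primary recovery has no room-air condition, allows a lymphocyte-only route and has no single time frame, so patients on oxygen or who later deteriorate can count as recovered

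*Protocol*

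**What the plan says.** **Endpoint.** Study outcome measures, Primary outcome, Phase II, defines recovery as the proportion in each group with normalization of fever and oxygen saturation, with "criteria for normalization: temperature < 38°C armpit, and SpO2 > 94%, sustained for at least 24 hours". It then adds a second route: "or lymphopenia recovery through Day 14". No oxygen condition is attached to the saturation limit. Nothing is said about relapse, escalation of support or death after the criterion has been met.

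**Entry.** The phase II inclusion criterion sets saturation at or below 94% "on room air at screening, requiring or not oxygen supplementation (nasal cannula, oxygen mask with reservoir, non-invasive ventilation, etc), but" excludes mechanical ventilation. The same cut-off is therefore tied to room air at entry and to no oxygen condition at outcome. Fever is not an entry requirement.

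**Measurement.** Daily Study Assessments record saturation at rest (or PaO2), with FIO2 and the oxygen device as separate items. These run until discharge and as far as workload permits.

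**Time frame.** Four places describe it:
- Primary outcome, Phase II: "through Day 14".
- Statistical analysis: "The crude probability of recovery at 14^th^ day will be compared by Chi-Square test".
- Table 3 (Schedule of activities phase II): the row "Evaluation of patient recovery" is marked once, in the Day 14 column.
- Data analysis, General considerations: "Recover incidence (RI): Time to recovery".

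**The concern.** A saturation above 94% means different things on room air and on a reservoir mask. Phase II enrols patients on substantial support, so the literal criterion can be met by the oxygen and not by any change in the disease. For an afebrile patient it could be met from baseline. The trial is open label, so the oxygen setting is in the hands of staff who know the allocation.

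The lymphocyte route has the same weakness in another form: it asks nothing about saturation.

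The time-frame wording matters because a cumulative endpoint and a status endpoint classify late deterioration in opposite ways. This is the primary outcome, so the definition fixes both what is tested and what the sample size ought to refer to.

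**Working it through.** **1. Three patients against the text**

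| Patient | Endpoint as worded | With room air required, or status taken at Day 14 |
| --- | --- | --- |
| Afebrile, at or below 94% on room air, held above 94% by oxygen for 24 hours | Recovered | Not recovered by the saturation route |
| Still at or below 94% on room air, lymphocyte count no longer below 1.2 × 10⁹/L by Day 14 | Recovered by the second route | Still recovered unless that route is changed |
| Normal for 24 hours on Day 3, dies on Day 10 | Recovered if the endpoint is cumulative through Day 14 | Not recovered if status is taken at Day 14 |

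The first two rows apply under any time frame. The third arises only from the cumulative reading. A time-to-recovery reading would give the third patient an event around Day 3.

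**2. The plan's sample size**

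Inputs from Sample Size: one-sided α = 0.05, power 80%, p₁ = 0.45, p₂ = 0.45/0.7 = 0.6429.

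n = [z₀.₉₅ √(2p̄(1−p̄)) + z₀.₈₀ √(p₁(1−p₁) + p₂(1−p₂))]² / (p₂−p₁)², with p̄ = 0.5464

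= [1.645 × 0.7041 + 0.842 × 0.6907]² / 0.1929² = 81.3, so 82 per compared group.

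This reproduces the stated 82. The sample-size arithmetic is not in question here.

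**3. Illustration of dilution**

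The documents give no figure for misclassification. Assume that a share q of patients who would otherwise be non-recovered is counted as recovered, equally in both groups. Each rate becomes p + q(1−p), and the difference shrinks by the factor (1−q). For q = 25%:
- SoC: 0.45 + 0.25 × 0.55 = 0.5875
- Intervention: 0.6429 + 0.25 × 0.3571 = 0.7321
- Difference: 0.1446 = 0.75 × 0.1929

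Power below is for the Pearson test at one-sided 0.05, summed over the exact binomial outcomes.

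| q (assumed) | SoC | Intervention | Power, 82 v 82 | Power, 41 v 41 |
| --- | --- | --- | --- | --- |
| 0 | 45.0% | 64.3% | 80% | 54% |
| 10% | 50.5% | 67.9% | 73% | 48% |
| 25% | 58.8% | 73.2% | 63% | 40% |
| 50% | 72.5% | 82.1% | 44% | 28% |

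The last column is there because the protocol gives 82 patients per arm and Subject Treatment Assignment randomizes 1:1 within each HLA arm. Read literally, that is 82/2 = 41 per compared group. Which reading is intended is a separate question.

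**The case against.** **Normalization.** All patients enter at or below 94% on room air, so normalization could be read as a return above that limit on the same measure. That is a sensible intention, and it weakens any claim that patients will routinely be recovered at Day 0. However, the bracket that states the criteria does not say it, and the daily measurement instruction does not supply it.

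**Time frame.** Recovery at the 14th day can mean the cumulative proportion recovered by then, with the single Day 14 mark showing when this is judged. That reading is available, so the sections are ambiguous and do not necessarily define different endpoints. A reader might infer from the General considerations fragment that the primary analysis is really time to event. The fragment names no test and does not claim to replace the chi-square comparison, so that inference is not supported.

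**Deferral to a SAP.** Handling of relapse or death after response is often left to a SAP. That covers detail. It does not cover the oxygen condition or the choice between cumulative and point-in-time recovery, because the protocol itself fixes the primary endpoint.

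**Requiring the criterion still to hold at Day 14.** A reader might think this is the only cure. It is one design preference: a by-Day-14 endpoint on room air also removes the oxygen defect. It also needs Day 14 data that are not guaranteed, because Follow-up makes ambulatory visits after discharge discretionary and the promised telephone contacts are at Days 30 and 90.

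**Size.** The share q has no source, and equality between groups is assumed. The 45% comes from planning around recovery on the WHO ordinal scale, a different endpoint. All of this stands.

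**Conclusion.** The point holds for the definition as written. The saturation criterion lacks the room-air condition that entry carries at the same cut-off, and the lymphocyte route can classify a still-hypoxic patient as recovered. The time frame is inconsistent enough that a patient who normalises briefly and then deteriorates or dies before Day 14 can be counted either way.

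The power figures show how sensitive the comparison is; they do not estimate what will happen. They rest on an assumed q that is equal in both groups, on planning rates taken from another endpoint, and on 82 (or 41) per compared group. It would be tempting to infer that the trial loses a known amount of power, but the documents do not support that. If q differed between groups, which open-label oxygen management makes possible, the bias could go in either direction.

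**What to change.** In Primary outcome, Phase II:
- Require SpO2 above 94% on room air, with no supplemental oxygen or ventilatory support, for at least 24 hours. This classifies recorded status and asks for no change in oxygen management.
- State one time frame, either by Day 14 or at Day 14, and use it in Statistical analysis, Table 3 and General considerations.
- Count patients who die by Day 14 as not recovered, and say how deterioration after meeting the criterion is classified.
- State explicitly whether lymphocyte recovery alone still qualifies. Dropping or keeping that route changes the composite, so the sponsor should decide it openly.
- If at Day 14 is chosen, give a rule for patients discharged earlier.

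The cost is a protocol amendment to the endpoint wording. FIO2 and oxygen device are already scheduled daily until discharge, as far as workload permits, so the room-air condition needs no new assessment. A status at Day 14 would need either a rule or a firm contact for discharged patients. The expected recovery rate will be lower in both groups than under the present wording, so the planning rates should be checked against the revised definition.

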## Secondary outcomes:

- Time (days) to normal level of lymphocytes.
- Proportion of patients showing clinical improvement at day 7 according to the investigator (based on respiratory status and blood-result tests).
- Proportion of patients receiving a second cycle.
- Time (days) to first negative SARS-CoV-2 PCR after infusing adoptive NK cells or adoptive memory T cells.
- The incidence of treatment-related adverse events (new or worsening from baseline) will be summarized by system organ class and/or preferred term, severity, type of adverse event and relation to study treatment. They will be defined by the Common Terminology Criteria for Adverse Events (CTCAE) Version 5.0
- Duration (days) of hospitalization.
- Time (days) to discharge or to a NEWS (Appendix 1) of ≤ 2 and maintained for 24 hours, whichever comes first.
- Time to improvement by one category on a 7-point ordinal scale (Appendix 2).
- Subject clinical status (on a 7-point ordinal scale) at day 14.
- Proportion of patients requiring intensive care unit.
- All-cause mortality at Day 28.

## Exploratory outcomes:

- To determine donor chimerism by short tandem repeats and a variable number of tandem repeat markers using the ABI Prism 3130 System and immune lymphocyte reconstitution by multiparametric flow cytometry after adoptive therapy weekly during the first month after infusion.
- Immune reconstitution: Immunoglobulins, serum cytokines (IL-6, IL-1, TNFa, IFNb, IL-10); T cell repertoire: CD3 (CD4, CD8), naive CD45RA+CD27+, central memory CD45RA-CD27+, effector memory CD45RA-CD27- y EMRA CD45RA+CD27-, Activated T cells (HLADR+), T regs (CD4+CD25+CD127low), Tgd; NK cells repertoire CD56+CD3- (KIR (2DL1, 2DL2/3, 3DL1), NCR (NKp30, NKp44, NKp46), NKG2D); NKT cells, B cells, memory B cells (CD19+CD27+).

#

1. SAFETY MONITORING AND REPORTING

## DEFINITIONS

**Adverse event (AE):**

Any untoward occurrence harmful to the health of a patient or clinical trial subject treated with a medicinal product and which does not necessarily have a causal relationship with the study treatment.

Abnormal laboratory values or test results constitute AEs only if they fulfill at least one of the following criteria:

- they induce clinical signs or symptoms
- they are considered clinically significant
- they require treatment

**Adverse Reaction (AR):**

An AR is any harmful and unintended reaction to an investigational medicinal product, regardless of the dose administered.

**Serious Adverse Event (SAE) and Serious Adverse Reaction (SAR):**

A serious adverse event is any untoward medical occurrence that at any dose:

- Results in death,
- Is life-threatening (NOTE: The term "life-threatening" in the definition of "serious" refers to an event in which the participant was at risk of death at the time of the event; it does not refer to an event which hypothetically might have caused death if it were more severe),
- Requires inpatient hospitalization or prolongation of existing hospitalization,
- Results in persistent or significant disability/incapacity, or
- Is a congenital anomaly/birth defect.
- Other important medical events. NOTE: Other events that may not result in death are not life threatening, or do not require hospitalization, may be considered a serious adverse event when, based upon appropriate medical judgment, the event may jeopardize the patient and may require medical or surgical intervention to prevent one of the outcomes listed above.

The concept "requires hospitalisation" would exclude both hospitalisation planned for scheduled treatment as well as those that were planned or envisaged before the study started in connection with a pre-existing medical condition.

All malignant neoplasms will be assessed as serious under “medically significant” if other serious criteria are not met and the malignant neoplasm is not a disease progression of the study indication.

Any suspected transmission via a medicinal product of an infectious agent is also considered a serious adverse reaction.

## CLASSIFICATION OF AN ADVERSE EVENT

**Severity of an Event**

Adverse events will be assessed and graded according to the Common Terminology Criteria for Adverse Events (CTCAE) version 5.0. If CTCAE grading does not exist for an AE, the severity of mild, moderate, severe, life-threatening and fatal, corresponding to Grades 1-5, will be used.

**Relationship to Study INTERVENTION**

All adverse events (AEs) must have their relationship to study intervention assessed by the clinician who examines and evaluates the participant based on temporal relationship and his/her clinical judgment. The degree of certainty about causality will be graded using the categories below. In a clinical trial, the study product must always be suspected.

- **Related** – The AE is known to occur with the study intervention, there is a reasonable possibility that the study intervention caused the AE, or there is a temporal relationship between the study intervention and event. Reasonable possibility means that there is evidence to suggest a causal relationship between the study intervention and the AE.
- **Not Related** – There is not a reasonable possibility that the administration of the study intervention caused the event, there is no temporal relationship between the study intervention and event onset, or an alternate etiology has been established.

**Expectedness**

Investigators will be responsible for determining whether an adverse event (AE) is expected or unexpected. An AE will be considered unexpected if the nature, severity, or frequency of the event is not consistent with the risk information previously described for the study intervention.

**Unexpected adverse reaction:**

An adverse reaction, the nature or severity of which is not consistent with the applicable product information.

**Suspected Unexpected Serious Adverse Reaction (SUSAR):**

Serious adverse drug reaction (SAR) that is unexpected or for which the development is uncommon (unexpected issue) observed during a clinical trial and for which there is a relationship with the study drug.

These adverse drug reactions, characterized to be serious and unexpected, need to be communicated immediately (mandatory) in accordance with national legislation and international guidelines.

## INFORMATION ON ADVERSE EVENTS

The investigator will monitor and systematically collect the AEs starting from the signing of the Informed Consent Form until the final follow-up visit of each subject.

The occurrence of AEs must be sought by non-directive questioning of the subject at each visit during the study. Adverse events may also be detected through physical examination findings, laboratory test findings, or other assessments.

Also, the investigator will assess and record, in detail, the AE, including the start and end dates, the description of the event, severity, course, outcome, the relationship of the AE with the investigational medicinal product and the measures taken (treatments, additional complementary examinations, etc.).

The AE will be recorded in the medical history and recorded in the Case Report Form.

The subjects who present with an AE will be subjected to relevant follow-up until its resolution or until it is judged to be permanent. The type of follow-up will be conducted according to the relevant criteria depending on the particular event.

## SAE REPORTING

If an SAE is produced, the investigator shall notify the sponsor or whoever assumes the tasks delegated by the sponsor, within a maximum period of 24 hours from the time of knowing about the event.

Also, the investigator shall complete and sign the SAE report form and send it by fax or email to:

**[contact]**

**Person Responsible For Pharmacovigilance**

**Unidad Central de Investigación Clínica y Ensayos Clínicos (UCICEC)**

**Hospital Universitario La Paz**

**[name]**

**[name]**

**[contact]/[contact]**

The sponsor or whoever assumes the tasks delegated by the sponsor will review the received form and, if necessary, request additional information from the investigator. The investigator will provide information to the sponsor or whoever assumes the tasks delegated by the sponsor, whenever asked and, in all cases, when the initial assessment changes in severity or causality. To communicate the follow-up information, repeat the reporting procedure described previously.

The sponsor, or whoever assumes the tasks delegated by the sponsor, shall keep detailed records of all the SAEs or the events of special interest, which are notified by the investigators.

In the case of a medication error or if the investigational medicinal product is used outside the provisions of the protocol, while conducting the study, the investigator shall notify the sponsor or whoever assumes the tasks delegated by the sponsor, within 24 hours from the time of knowing about the event. The reporting circuit and form will be the same as for the SAE.

